# Effectiveness of a multifactorial falls prevention program in community-dwelling older people when compared to usual care: study protocol for a randomised controlled trial (Prevquedas Brazil)

**DOI:** 10.1186/1471-2318-13-27

**Published:** 2013-03-15

**Keywords:** Accidental falls, Clinical trial, Aged, Exercise, Education

## Abstract

**Background:**

Falling in older age is a major public health concern due to its costly and disabling consequences. However very few randomised controlled trials (RCTs) have been conducted in developing countries, in which population ageing is expected to be particularly substantial in coming years. This article describes the design of an RCT to evaluate the effectiveness of a multifactorial falls prevention program in reducing the rate of falls in community-dwelling older people.

**Methods/design:**

Multicentre parallel-group RCT involving 612 community-dwelling men and women aged 60 years and over, who have fallen at least once in the previous year. Participants will be recruited in multiple settings in Sao Paulo, Brazil and will be randomly allocated to a control group or an intervention group. The usual care control group will undergo a fall risk factor assessment and be referred to their clinicians with the risk assessment report so that individual modifiable risk factors can be managed without any specific guidance. The intervention group will receive a 12-week *Multifactorial Falls Prevention Program* consisting of: an individualised medical management of modifiable risk factors, a group-based, supervised balance training exercise program plus an unsupervised home-based exercise program, an educational/behavioral intervention. Both groups will receive a leaflet containing general information about fall prevention strategies. Primary outcome measures will be the rate of falls and the proportion of fallers recorded by monthly falls diaries and telephone calls over a 12 month period. Secondary outcomes measures will include risk of falling, fall-related self-efficacy score, measures of balance, mobility and strength, fall-related health services use and independence with daily tasks. Data will be analysed using the intention-to-treat principle.The incidence of falls in the intervention and control groups will be calculated and compared using negative binomial regression analysis.

**Discussion:**

This study is the first trial to be conducted in Brazil to evaluate the effectiveness of an intervention to prevent falls. If proven to reduce falls this study has the potential to benefit older adults and assist health care practitioners and policy makers to implement and promote effective falls prevention interventions.

**Trial registration:**

ClinicalTrials.gov (NCT01698580)

## Background

The increase in non-communicable diseases (NCDs), including fall-related injuries, will be a major challenge in a progressively more globalized, urban and ageing world, especially in developing countries [1,2]. Falling in older age is a major public health concern due to the immediate injury-related consequences, such as fractures and traumatic brain injuries, but also due to the risk of associated long term disability, costly hospitalisations and subsequent nursing home admission [3,4]. One third of older adults aged 65 years and older fall at least once each year. This rate increases substantially with increasing age, and around 50% of people aged 80 years or more experience a fall event each year [5-7]. Brazilian cohort studies have shown similar rates [8,9].

Between 2% and 6% of falls result in fracture and the most common is hip fracture, [10] which is related with functional decline, death and increase in hospitalization costs [11]. Approximately 40% of total hospitalisations in the Brazilian public health system in 2009 were due to injury-related accidents [12]. A large cross-sectional study, using data from the Brazilian National Injury Surveillance System, revealed that among those aged 60 years and over emergency visits due to falls were associated with a reported disability [13].

Falls result from an interaction between environmental hazards and inadequate physiology to cope with the hazards, such as gait problems, poor vision, impaired peripheral sensation and lower limb strength, dizziness, and the use of psychotropic medication or polypharmacy [14,15]. Guidelines recommend a multifactorial fall risk assessment for all older adults who present for medical attention after a fall or who have gait or balance problems [16]. This assists with the identification of modifiable risk factors and with the implementation of targeted interventions for falls prevention [4]. The delivery of effective interventions for preventing falls in usual clinical practice presents a challenge for policy makers and health professionals [17,18].

A recent Cochrane review on falls prevention for older people living in the community included 111 randomised controlled trials (RCTs), with a total of 55,303 participants [19]. However, only four studies were conducted in developing, low-income countries [20-23]. The vast majority of RCTs have been conducted in developed countries, such as United States, Canada and Australia. This systematic review identified that multifactorial intervention, as well as exercise alone, either delivered as a multiple-component group exercise or home-based exercise, reduce fall rates but only exercise reduced risk of falls. Another systematic review has shown that exercise reduced the rate and risk of falling and there was a greater relative effect on fall rates observed in programs that included a combination of a higher dose of exercise (50 hours or more), progressive balance-challenging exercises and no walking program [24].

It has been recognised that multifactorial interventions that actively provide treatments aimed at reducing risk factors are more effective than those that provide referral and information alone [3,25]. Furthermore, existing trials of multifactorial programs are quite heterogeneous and different results in terms of fall rate reductions may be due to differences in participants’ sociocultural backgrounds, health care system characteristics and structures [19].

The aim of this study is to evaluate the efficacy of a multifactorial falls prevention intervention, composed of individualised risk factor management, exercise and educational/behavior change sessions, in reducing fall rates, in community-dwelling older adults living in Brazil when compared to usual care.

## Methods

### Trial design

This study is a multicentre parallel-group RCT with 12 months follow-up (Figure 1). The Human Ethics Committee of the University of São Paulo Faculty of Medicine Clinics Hospital (CAPPesq 0145/11) has approved the trial and all participants will give written informed consent. Participants will be randomly allocated to either a “usual care” control group or the ‘multifactorial falls prevention program” intervention group. Eligible participants will be randomly allocated to study groups after the completion of a baseline assessment. The maximum estimated length between the baseline assessment and the randomisation will be 3 months.Group allocation will take place centrally using a computer-generated permuted block randomisation schedule by an investigator not otherwise involved in recruitment or data collection (i.e., a concealed randomisation system). Assessors will be blinded to group allocation but due to the nature of the trial, the participants will not be blinded to group allocation.

**Figure 1 F1:**
[figure not shown]
Design of study.

### Participants

Community-dwelling men and women aged 60 and over who have fallen at least once in the last 12 months will be included. A fall will be defined as “an unexpected event in which the participants come to rest on the ground, floor, or lower level.” Participants will be asked to answer the question: “In the past 12 months, have you had any fall including a slip or trip in which you lost your balance and landed on the floor or ground or lower level?” [26].

At initial contact potential participants will be screened by telephone to ensure they have fallen at least once in the past 12 months and will be able to attend the evaluation centre once a week for 12 weeks. If there is an affirmative answer to both questions, the person will be invited to attend the evaluation centre to be assessed for eligibility.

Participants will be excluded if they have:

• A previous diagnosis of dementia or a cognitive decline that prevents the understanding of simple instructions or guidelines;

• A previous stroke with a severe neurological impairment, such as loss of strength, and perceptual or language limitations;

• A progressive neurological disease (e.g. severe Parkinson’s disease);

• A severe visual deficiency;

• Any acute illness that the physician considers as an exercise contra-indication (e.g. uncontrolled angina, acute coronary disease);

• An acute vertigo or dizziness less than3 months duration;

• Inability to maintain a standing position, even with the use of a walking aid or other device.

Participants will also be excluded if they unable to communicate due to an aphasia, severe hearing loss even with the use of hearing aids or those who do not have mastery in Portuguese language. People will also be excluded from participation if they are engaged in a regular exercise program that is likely to challenge balance, including physical therapy, with a frequency of equal to or more than twice a week such as: muscle strengthening, balance or gait exercise, Tai Chi and Yoga. People will not be excluded if their regular exercise regime is limited to walking, water-based exercise or any other form of therapy that does not include the exercises described above (e.g., thermotherapy, spine and shoulder exercises, etc.).

### Setting and recruitment

Participants will be recruited in 4 referral centers in Sao Paulo, Brazil (Geriatrics Service at the University of São Paulo Faculty of Medicine Clinics Hospital; the Institute of Geriatrics and Gerontology “José Ermírio de Moraes”; the Reference Centre for the Elderly in the North Zone and the Paula Souza Primary Care Centre).

The Faculty of Medicine Clinics Hospital is a public complex of health institutions which offers 2,200 beds, distributed between its six specialized institutes and also outpatient services and rehabilitation. The Institute of Geriatrics and Gerontology is located in a very populated area, the east zone of Sao Paulo and is reference for 41 primary health units. The Reference Centre for the Elderly in the North Zone covers 142 primary health care units. The Paula Souza Primary Care Centre is located in the west zone of São Paulo.

The intervention will be delivered in 3 sites: Geriatrics Service at the University of São Paulo Faculty of Medicine Clinics Hospital; the Institute of Geriatrics and Gerontology “José Ermírio de Moraes”; the Reference Centre for the Elderly in the North Zone, where a multidisciplinary team will be trained to deliver the program. Figure 1 describes the study design.

### Control group

The control group will receive a baseline assessment to identify risk factors for falls and will be referred to their clinicians with a report of individual modifiable risk factors to be managed without any specific guidance: referral to routine services or specific interventions will be at the discretion of their primary clinicians. So, further management of each participant in the control group will be individualised with no specific protocol. Interventions will be recorded. Participants will receive a leaflet with general information about fall prevention and instructions to fill in a monthly fall diary. They will be telephoned each month to ask for the information regarding falls and their consequences.

### Intervention group

The intervention group will also receive a baseline assessment to identify risk factors for falls and will be referred to their clinicians with a report of individual modifiable risk factors so they will be able to receive usual care until they start to attend the Multifactorial Falls Prevention Program. Participants will also receive a leaflet with general information about fall prevention. The Multifactorial Falls Prevention Program will be a 12 week group-based intervention for 10 to 12 participants per group, with two and a half hour session per week. Once a month, there will be an additional one hour medical evaluation. During the intervention period participants will also keep their regular visits to their primary care clinicians. Clinicians of each participant in the intervention group will be contacted and encouraged to motivate their patients to adhere to the program, especially the home-based exercises.

The program will consist of:

1. A progressive, structured, *on-site exercise program* consisting of specific balance and strengthening exercises delivered by trained physiotherapists, who will undergo a day-long training session and receive a training manual. The group-based program will be conducted on a weekly basis, and will last for an hour and a half each session. In addition a *home-based exercise program* will be performed twice a week at home. The physiotherapists who will deliver the on-site group-based program will also teach the home-based exercises.

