2. Educational/behavioural sessions addressing specific environmental and behavioural risk factors for falls will be delivered by trained health professionals. The 12 educational sessions will last for 40 minutes each and will use appropriate language for lay people. Audio-visual material will be used to support the verbal content when appropriate. Each meeting will consist of a brief introduction to the core topic for the day with supporting audio-visual or graphical material. This will be followed by group discussion to identify the beliefs, experiences and attitudes of participants regarding the discussion topic and any major barriers to the implementation of the suggested preventive strategies. In addition to discussing intervention strategies from the point of view of fall prevention, other benefits will be highlighted, such as for general health and improving or maintaining functional independence. The educational session will always end with a summary of the core messages of the session. Topics to be covered in the sessions are included in Table 1. The health care professional responsible for delivering the educational/behavioural sessions will attend a one-day training session and will receive a manual containing the specified core components of each session, learning strategies, goals to be achieved and messages to be delivered to participants.

3. A medical evaluation of modifiable risk factors not amenable to exercise will be performed by trained doctors, based on the currently available evidence [16]. The following risk factors will be addressed:

i. Postural hypotension

Participants with postural hypotension will be recommended to use pressure stockings and will receive counselling on associated behavioural factors, such as adequate fluid intake, sleeping with an elevated head, avoiding sudden changes in position and making circular movements with the feet before standing up. A review will be conducted into the use of medications that may contribute to postural hypotension such as antihypertensives, alpha agonists and tricyclic antidepressants and a contact with the primary care physician will be made to discuss any medication withdrawal. In regards to postprandial hypotension, participants will be encouraged to eat small, frequent meals, and to lie down after each meal.

ii. Visual impairment

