### Sample size calculation

A total of 612 participants (306 per group) will provide 80% power to detect as significant, at the 5% level, a 30% lower rate of falls (i.e. the primary outcome measure) for intervention group participants compared with control participants (i.e., IRR = 0.70). For the sample size calculation we used the gennbreg command in Stata and coefficients from previous studies: alpha (a measure of over-dispersion in the negative binomial regression model) was assumed to be 0.76 based on data from a previous trial [43]. We assumed the control group rate of falls would be 1 fall per person over the 12-month follow-up period. An average follow-up period of 11 months (rather than the planned 12 months) was used in these calculations to account for loss to follow-up.

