### Statistical analysis

The primary analyses will be conducted using the intention-to-treat principle. Fall data will be analysed using all randomised participants until they have died or have withdrawn from the study. Demographic and clinical characteristics at baseline will be summarized with descriptive statistics. The incidence of falls with 95% confidence intervals (CIs) in the two groups (intervention group and control group) will be calculated and compared using negative binomial regression analysis. The proportion of fallers in the two groups will be compared with the relative risk statistic. General linear models will be used to assess the effect of group allocation on the continuously-scored secondary outcome measures after adjusting for baseline scores. Logistic regression models will be used to compare groups on dichotomous outcome measures. Interactions between subgroup variables (past falls and mobility-related disability) and group allocation will be tested, and in the case of a significant interaction, the comparison between the intervention group and control group will be reported within the subgroups. Statistical analyses will be undertaken using the SPSS and Stata software packages. P < .05 will be considered statistically significant.

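### The sample size and the named fall-rate model make no allowance for group delivery in the intervention arm; if effects differ between groups, the interval is somewhat too narrow

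*Protocol article*

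**What the plan says.** - **Randomisation** is of individuals (Trial design): "Group allocation will take place centrally using a computer-generated permuted block randomisation schedule".
- **Intervention arm** (Intervention group): the program "will be a 12 week group-based intervention for 10 to 12 participants per group". The physiotherapists who run the classes also teach the home exercises. Each educational session opens with a short introduction, and then: "This will be followed by group discussion to identify the beliefs, experiences and attitudes of participants".
- **Control arm** (Control group): "further management of each participant in the control group will be individualised with no specific protocol". There are no delivery groups.
- **Sample size** (Sample size calculation): "A total of 612 participants (306 per group) will provide 80% power" to detect, "at the 5% level, a 30% lower rate of falls". The other listed inputs are one fall per control participant over 12 months, 11 months of average follow-up, and over-dispersion: "alpha (a measure of over-dispersion in the negative binomial regression model) was assumed to be 0.76". No ICC, group size or design effect is listed.
- **Analysis** (Statistical analysis): the incidence of falls in the two groups, with 95% confidence intervals, "will be calculated and compared using negative binomial regression analysis". Fallers are compared by relative risk, and secondary outcomes by general linear and logistic models. None is described with a term or variance for delivery group.

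**The concern.** This is a partially nested design: about 28 delivery groups (306/11) in one arm and single individuals in the other. Members of a group share a physiotherapist, an educator and 12 weeks of discussion with the same peers. If some groups are led or progressed better than others, their members' fall counts will be positively correlated. The over-dispersion parameter describes variation between persons. It does not describe correlation between members of the same group, so a standard negative binomial fit leaves that component out of the variance of the intervention-arm rate.

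At stake is the width of the primary confidence interval and, for a borderline result, how far the p-value can be trusted. The balance and strength measures among the secondary outcomes are exposed in the same way, since they are what the classes train.

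**Working it through.** **Inputs from the protocol.** Control rate 1 per year; rate ratio 0.70; over-dispersion k = 0.76; follow-up t = 11/12 = 0.917 year; 306 per arm; 5% level (sidedness not stated; two-sided taken); group size m = 10 to 12 (11 used). **Assumed:** the ICC, shown as a range.

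**Step 1: the plan's own figure, without clustering.** Per-participant variance of the log rate:
- control: V0 = 1/0.917 + 0.76 = 1.851
- intervention: V1 = 1/(0.70 × 0.917) + 0.76 = 2.318

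n per arm = (1.96 + 0.842)² × (V0 + V1)/(ln 0.70)² = 7.849 × 4.169/0.1272 = 257.2, so 258 per arm or 516 in total. The stated 612 is not reproduced. At 306 per arm the formula gives 86.3% power, not 80% (simulation 85% to 87%). Why 612 exceeds 516 is a separate matter; here it only means that there is some slack.

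**Step 2: clustering in the intervention arm only.** Design effect DE = 1 + (m − 1) × ICC, applied to V1:
- ratio of true to naive SE at rate ratio 0.70 = √[(V0 + DE × V1)/(V0 + V1)]
- error rate under zero average effect (equal variances in the two arms) = 2 × [1 − Φ(1.96/√((1 + DE)/2))]
- power when correctly analysed = Φ(0.3567/√[(V0 + DE × V1)/306] − 1.96)

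Example at ICC 0.05: DE = 1.5. SE ratio = √(5.329/4.169) = 1.13. Error rate = 2 × [1 − Φ(1.96/√1.25)] = 8.0%. Power = Φ(0.3567/0.1320 − 1.96) = 77.1%.

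| ICC (assumed), m = 11 | DE | True SE / naive SE | Error rate, zero average effect | Correctly analysed power at 306 per arm |
|---|---|---|---|---|
| 0 | 1.0 | 1.00 | 5.0% | 86.3% |
| 0.01 | 1.1 | 1.03 | 5.6% | 84.5% |
| 0.02 | 1.2 | 1.05 | 6.2% | 82.6% |
| 0.03 | 1.3 | 1.08 | 6.8% | 80.8% |
| 0.05 | 1.5 | 1.13 | 8.0% | 77.1% |
| 0.10 | 2.0 | 1.25 | 11.0% | 68.8% |

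Group size matters little within the stated range: at ICC 0.05 the error rate is 7.7% with m = 10 and 8.3% with m = 12.

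**Step 3: simulation check.** Trials were simulated with a group effect in the intervention arm and analysed by an unadjusted maximum-likelihood negative binomial fit. With zero average effect (5,000 trials each), the rejection rate was 5.5%, 5.6%, 6.2% and 7.8% at ICC 0, 0.01, 0.02 and 0.05. At rate ratio 0.70 (2,000 trials each), coverage of the nominal 95% interval was 94.9%, 93.7%, 93.9% and 90.5%. Simulation error is about 0.3 and 0.5 percentage points respectively, and the results agree with the formulas to within about three such errors.

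**Step 4: the ICC that 306 per arm can absorb.** 80% power needs V0 + DE × V1 ≤ 306 × 0.1272/7.849 = 4.960. So DE ≤ (4.960 − 1.851)/2.318 = 1.341, and ICC ≤ 0.341/(m − 1). This is 0.038, 0.034 and 0.031 for m = 10, 11 and 12, or about 0.03.

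**The case against.** Five arguments weigh against the point.

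1. **No ICC is given.** A reader might infer that the interval is certainly too narrow and that the test certainly exceeds 5%. The protocol does not support that: both need an ICC above 0, and at 0.01 to 0.02 the effect is small. This stands, and the point is conditional because of it.
2. **Individual randomisation protects the strict null.** If the program affects no one, groups formed after allocation add no error to the test. The inflated error rates belong to a different null, in which effects average to zero but differ between groups. This stands for the test. It does not protect the interval when there is an effect, which is the case that the trial is planned around.
3. **Site and season are not sources of the problem.** Controls come from the same centres and periods. Only therapist, educator and peer effects are specific to the intervention arm. This stands.
4. **The larger ICCs imply large group differences.** With a per-person variance of 1.85, ICC 0.05 implies a between-group standard deviation in log fall rate of about √(0.05 × 1.85) = 0.30, against a whole planned effect of |ln 0.70| = 0.36. Staff training, manuals, individual prescription and home exercise all work against such spread. This makes 0.05 hard to presume, but it does not make the ICC zero: even 0.02 implies a standard deviation of only 0.19.
5. **An analysis plan may handle it.** The article names a model family and does not rule out robust variance, and an analysis plan that is not shown may specify one. So the protocol cannot be said to have decided against an adjustment. The sample size paragraph does list its inputs, however, and clustering is not among them.

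**Conclusion.** The point holds in conditional form, as an inexpensive improvement and not as a defect that invalidates the plan. Delivery is grouped in one arm only, and neither the sample size inputs nor the model as named allows for it. If intervention effects vary between groups, the naive interval is too narrow: by about 3% to 5% in standard error at ICC 0.01 to 0.02, and by about 13% at 0.05.

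This rests on an assumed ICC, groups of about 11, every intervention participant belonging to a group, and large-sample formulas. A reader might also infer that the trial is underpowered or needs more participants. On the stated inputs it is not, up to an ICC of about 0.03. That margin exists because 612 is more than those inputs require; the protocol does not present it as an allowance for clustering.

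**What to change.** 1. **Data.** Record the delivery group of every intervention participant. The trial is still recruiting, so this can be done now.
2. **Analysis.** In the primary fall-rate model, use either standard errors clustered on delivery group with a small-sample correction (there are only about 28 groups), or a random intercept for delivery group in the intervention arm only. Treat each control as a single unit. Under intention to treat, do the same for intervention participants never placed in a group. Apply the same approach to the comparison of fallers and to the secondary models.
3. **Sample size paragraph.** Add that, on its own inputs and with groups of 10 to 12, 306 per group keeps 80% power up to an ICC of about 0.03.

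The cost is one recorded field, a few sentences of text and a slightly wider interval. No more patients are needed.
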